### 9.1.4 Record of adverse events

The adverse event record form should be filled out truthfully during the test.

Its type, degree, occurrence time, duration, treatment measures, treatment after detailed records, in the comprehensive consideration of comorbidities, combined with the use of drugs based on the evaluation of its relevance to the test drug. All physical examinations and laboratory examinations required by the test plan should be recorded in the subjects' ECRF.

Comparing the results of physical examination, laboratory examination and pre-administration

examination results after drug administration, if the change suggested that the clinical status of the subjects deteriorated, the researcher must evaluate them to determine whether they were in line with the definition of adverse events and to record all changes that were identified as adverse event definitions in the adverse events section of eCRF.

Medical documents relating to adverse events should be recorded in the original document, including a report of laboratory examination results. Diagnostic or therapeutic invasive (such as surgery), non-invasive operations should not be credited as adverse events, and the disease that causes the operation should be documented as adverse events. Acute appendicitis, which occurs during adverse events reporting, should be reported as adverse events, and therefore appendectomy should be documented as a treatment for this adverse event.

### **9.1.5 Treatment and follow-up of adverse events**

In the event of adverse events, whether there is a causal relationship between the incident and the test drug, should be actively dealt with. Patients who experience adverse events should be treated with acceptable clinical treatment measures.

If it is necessary to apply the medical measures rejected by the study, the applicant should be consulted whether the patient withdrew from the trial.

Adverse events should be followed up continuously until one of the following conditions is met:

- 1) resolved;
- 2) The event is stable;
- 3) The incident returns to the baseline level;
- 4) The event may be attributed to a drug other than a test drug or is unrelated to the test behavior;
- 5) When more information is impossible to obtain (the subject refuses to provide more information, or there is evidence that the participant is still missing after the best effort).

## **9.2 Serious adverse event**

### **9.2.1 Definition of serious adverse events**

A serious adverse event is defined as any adverse experience that meets any of the following criteria:

- 1) Results in death;
- 2) Is life-threatening;
- 3) Requires hospitalization or prolongation of existing hospitalization.
- 4) Results in persistent or significant disability or incapacity
- 5) Teratogenic, birth defects

6) Important medical events that may not result in death, be life-threatening, or require hospitalization may be considered serious when, based upon appropriate medical judgment, they may jeopardize the patient or subject and may require medical or surgical intervention to prevent one of the outcomes listed in this definition.

Note:

- 1) Life threatening indicate that the risk of imminent death of a serious patient, not the assumption that serious event will develop to death in the future.
- 2) Prolonged hospitalization or hospitalization not including the following situations:
  - Management reasons for hospitalization (e.g. annual medical examinations);
  - Routine admissions in ER (eg, admitted overnight for fluid resuscitation)
  - Due to the chronic disease admission, there is no new adverse reactions, there is no worsening of the original disease (in order to check the chronic laboratory abnormalities);
  - hospitalization was followed the protocol's required during the clinical trial (as required by the protocol);
  - Prior to the study, the subjects were already diagnosed with from some type of disease, the symptoms did not get worse, but already planned ahead to hospitalization and/or undergoing surgical procedures in the course of the study (e.g. elective cosmetic surgery)
  - Hospitalization solely for the transfusion of blood products
  - Hospitalization for normal delivery
  - The other situation that Investigator don't think need to be hospitalized

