### 9.2.2 Processing and recording report of serious adverse events

In the event of any serious adverse event occurring in the trial, whether the incident is related to the trial and the test drug, whether it be an initial report, a follow-up report or a summary report, the investigator should immediately evaluate the incident and complete the report form of the serious adverse event, sign and date,

Within 24 hours of being notified to Shandong Luye Pharmaceutical Co., Ltd. or designated CRO, Ethics Committee, the State Drug Administration, the National Health and Health Committee, the pilot unit of the Provincial Drug Administration department.

The relevant contact information for reporting SAE is as follows:

| Reporting unit | phone        | fax          | public postboxes        | address                                 |
|----------------|--------------|--------------|-------------------------|-----------------------------------------|
| Shandong Luye  | [name] | [name] | [contact] | [name] |

|                                                |                                              |                              |    |                                                                                                                                                                                                 |
|------------------------------------------------|----------------------------------------------|------------------------------|----|-------------------------------------------------------------------------------------------------------------------------------------------------------------------------------------------------|
| Pharmaceutical Co., Ltd. or its designated CRO |                                              |                              |    | [name]                                                                                                                                  |
| State Drug Administration                      | [name]
[name]
[name] | [name]                 | no | [name]                                                                                                                 |

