#### **11.2.2.5 Safety evaluation**

Adverse events will be coded using MedDRA. The statistical analysis will be focus on treatment emergent adverse events (TEAE), The adverse events that occurred from the screening to the first dose will be presented by listing, but not included in the statistical analysis of adverse events. Adverse events mentioned in the following paragraphs are all for TEAE.

All adverse events, adverse events related to the study drug, adverse events unrelated to the study drug, serious adverse events, and adverse events leading to withdraw will be summarized, number of subjects, frequency and percentage of subjects will be calculated, Fisher exact test will be used for statistical comparison. The TEAE and related TEAE categorized by SOC and PT will be summarized by treatment group. All adverse events, adverse events related to the study drug, adverse events unrelated to the study drug, serious adverse events, and adverse events leading to withdraw will also be presented by listings.

Shift tables will be used to summarize the clinical significance evaluation of laboratory and ECG parameters, and all abnormal parameters with clinical significance will be listed.

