#### **11.2.2.9 Data Monitoring Committee**

The data monitoring committee will not be set up for this clinical trial.

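### The last exception in the serious adverse event definition lets an actual hospital admission for an adverse event be declassified on the investigator's opinion alone

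*Protocol*

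**What the plan says.** Section 9.2.1 of the protocol lists six criteria, any one of which makes an adverse event serious. The third is "Requires hospitalization or prolongation of existing hospitalization".

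Note 2 under that list narrows the third criterion. It opens "Prolonged hospitalization or hospitalization not including the following situations" and gives eight bullets. Seven describe an identifiable kind of admission: administrative, routine emergency-room, chronic disease, required by the protocol, planned before the study, for transfusion only, and for normal delivery. The eighth reads "The other situation that Investigator don't think need to be hospitalized".

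Two later sections depend on the classification. Section 9.2.2 sets out the form and the 24-hour notification, and begins "In the event of any serious adverse event occurring in the trial". Section 11.2.2.5 says that "serious adverse events, and adverse events leading to withdraw will be summarized", with numbers and percentages of subjects and a Fisher exact test.

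**The concern.** A list of exceptions to the hospitalisation criterion is normal when each exception can be checked against the record. The last bullet cannot be checked in that way. It sets no condition on the event, gives no example and asks for no confirmation by the sponsor or anyone else. The only test is what the investigator thinks.

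This matters here because section 5.1 restricts entry to outpatients, so any admission is a change of status. Section 8.2.7 asks for close watch on worsening depression, suicidality, hypomania and mania, and admission is one way such an event becomes serious without being immediately life-threatening. If the admission is declassified, the event need not be sent within 24 hours to the sponsor, the ethics committee and the authorities, who are the parties in a position to question the judgement. Section 11.2.2.9 adds that "The data monitoring committee will not be set up for this clinical trial". The absence of a committee does not change how seriousness is classified, but it leaves expedited reports as one of the few routes by which such events reach people outside the site while the trial runs.

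**Working it through.** No arithmetic applies. The protocol gives no expected rate of serious adverse events or of admissions. The check sets the provisions side by side.

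1. **Criterion 3 against note 2 (9.2.1).** Criterion 3 brings in events that require or prolong a hospital stay. Note 2 takes listed situations out. An admission therefore counts under criterion 3 only if none of the eight bullets applies.

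2. **The bounded bullets.** The chronic-disease bullet applies only where "there is no new adverse reactions, there is no worsening of the original disease". The bullet on stays planned before the study likewise applies only if symptoms have not got worse. The other five are each tied to a stated purpose or setting of the admission. A monitor could verify all seven from source documents.

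3. **The last bullet against its neighbours.** Take a subject with a chronic disease who is admitted because it has worsened. The chronic-disease bullet does not apply, so criterion 3 would hold. The last bullet can still remove the admission if the investigator thinks it was not needed. It therefore undoes the limits built into the bullets above it. No other section of the protocol restricts it.

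4. **Criterion 6 as a safety net (9.2.1).** It begins "Important medical events that may not result in death, be life-threatening, or require hospitalization may be considered serious when" and turns on medical judgement. It may recover some excluded admissions, but it is permissive and the first decision lies with the same investigator. It is a partial safeguard and not an independent one.

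5. **What is kept and what is lost.**
   - Kept: the event is still an adverse event under 9.1.1, is recorded under 9.1.4, and enters the adverse event tables and listings of 11.2.2.5 if it is treatment-emergent. If it leads to withdrawal, it also appears in that separate summary. Death, life-threatening events, disability and birth defects remain serious whatever the bullet says.
   - Lost, unless another criterion applies: the serious adverse event form, the 24-hour report (9.2.2), and the event's place in the serious adverse event summary and listing (11.2.2.5).

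6. **Direction of the effect.** The bullet can take an event out of criterion 3 and can never put one in. The count of serious adverse events can only fall or stay the same. Because the test is opinion without stated criteria, two sites can classify the same kind of admission differently.

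**The case against.** The strongest reply is that criterion 3 says *requires*. Whether an event requires admission is already a medical judgement, so the last bullet may only state the converse: an admission that was not needed, for example for social reasons or convenience, was not required by the event. The protocol's English is rough throughout, and this may be all that was meant. Part of this stands. Criterion 3 does not make every admission serious, and it would be too strong to say that the bullet cancels it. But the bullet is written as a separate exclusion, applied to admissions that did take place, and sites will work from the words in front of them. If it only repeats criterion 3, deleting it loses nothing.

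A second reply is that safety detection does not depend on this classification. Adverse events are recorded regardless, the suicide scale is administered at every visit (section 7), and section 11.2.2.6 treats safety p-values as nominal. That is right, and it limits the point to classification, expedited reporting and the serious adverse event table.

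A reader might go further in two ways that the documents do not support.

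- **A size for the undercount.** Section 1 reports two *severe* events in Phase II, one hypomania and one worsening depression, and it is tempting to project that rate onto 558 subjects. Section 9.1.2 distinguishes severe from serious. Section 1 does not say that either patient was admitted, and both were in the 40 mg group, which is not studied here. Phase II also lasted 6 weeks against 8. No rate for this trial follows from it.
- **Bias between arms.** Investigators are blinded, so under-classification would be expected in all three arms. The protocol gives no ground for saying that it would favour one of them.

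**Conclusion.** The last bullet of note 2 is wrong as written. It is an unbounded exception to the hospitalisation criterion and is inconsistent with the conditions placed on the bullets beside it. Following the plan literally, an admission caused by a new or worsened adverse event can be left out of the serious adverse event form, the 24-hour report and the serious adverse event table on opinion alone.

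The direction is certain, because the count can only be lowered. The size cannot be estimated from the protocol. The expected harm is under-reporting and inconsistency between sites, with no demonstrated distortion of the comparison between arms. The conclusion assumes that sites apply the bullet as it reads in this English text; if the source-language wording is narrower, the English should be brought into line with it.

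**What to change.** Delete the last bullet of note 2 in section 9.2.1. The seven specific exceptions stay.

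If the sponsor wants to keep a residual category, limit it to admissions with no medical need arising from a new or worsened adverse event, and give examples such as admission for social reasons or convenience. In either case, ask for the investigator's view of whether the admission was needed in the event narrative, so that the opinion is kept without deciding the classification.

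The change affects reporting only and leaves clinical care untouched. It costs one line of text and possibly a few more serious adverse event reports.

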### 9.2.2 Processing and recording report of serious adverse events

In the event of any serious adverse event occurring in the trial, whether the incident is related to the trial and the test drug, whether it be an initial report, a follow-up report or a summary report, the investigator should immediately evaluate the incident and complete the report form of the serious adverse event, sign and date,

Within 24 hours of being notified to Shandong Luye Pharmaceutical Co., Ltd. or designated CRO, Ethics Committee, the State Drug Administration, the National Health and Health Committee, the pilot unit of the Provincial Drug Administration department.

The relevant contact information for reporting SAE is as follows:

| Reporting unit | phone        | fax          | public postboxes        | address                                 |
|----------------|--------------|--------------|-------------------------|-----------------------------------------|
| Shandong Luye  | [name] | [name] | [contact] | [name] |

|                                                |                                              |                              |    |                                                                                                                                                                                                 |
|------------------------------------------------|----------------------------------------------|------------------------------|----|-------------------------------------------------------------------------------------------------------------------------------------------------------------------------------------------------|
| Pharmaceutical Co., Ltd. or its designated CRO |                                              |                              |    | [name]                                                                                                                                  |
| State Drug Administration                      | [name]
[name]
[name] | [name]                 | no | [name]                                                                                                                 |

## 9.3 Pregnancy

### 9.3.1 Pregnancy treatment and record report

From subjects that have signed the informed consent to the last follow-up visit, if female subjects or male subjects' partner becomes pregnant during the course of the study, the investigator or other site personnel must be informed immediately, the investigator should record the event in the source document, and complete the pregnancy report form, signed and dated. Report to Shandong Luye Pharmaceutical Co., Ltd. Representative or the designated CRO and the Ethics Committee of the Research Center within 24 hours.

The investigator should also discuss the risk of continuing pregnancy and the effects to the fetus with the female subjects or male subjects' partners

### 9.3.2 Follow-up of pregnancy

All pregnancy events should be followed to the end of the pregnancy, i.e. termination of pregnancy or childbirth. if childbirth, should be follow-up to 42 days after the birth of the newborn. The investigator should keep updating the pregnancy report form, sign and dated based on any important information reported during pregnancy, and report it to Shandong Luye

Pharmaceutical Co., Ltd. or the designated CRO and the Ethics Committee of the Research Center within 24 hours.

If the subject appears to have any pregnancy-related SAE after completing the study, which is may be related to the study drug by the clincial judgement of researcher, it must be reported to Shandong Luye Pharmaceutical Co., Ltd. immediately.

Pregnancy events is not regarded as SAE, however outcome of pregnancy such as ectopic pregnancy, spontaneous abortion, intrauterine fetal demise, neonatal death, or congenital anomaly in a live born, a terminated fetus, an intrauterine fetal demise, or a neonatal death must be reported and handled as SAEs.

The outcomes of pregnancy or other medical events that meet SAE definitions should be reported and handled as SAE.

## 10. Unblinding

Emergency unblinding procedures: in order to protect the well being and safety of the trial subject, the coding system for the investigational medical product in blinded trials should include a unblinding code that permits rapid identification of the product in case of emergency unblinding is deemed to be necessary. Each unblinding code only can be used once and then become invalidated. There is a system in place for 24-hour cover to access the emergency unblinding. (login URL <http://jm.epiedc.com>) Follow the prompt operation for emergency uncovering. The investigator should use the system for emergency unblinding through the online blinding system as the main system. Each centre is also provided the sealed envelopes with appropriate code for emergency unblinded, which are kept in center. If serious adverse event or death or emergency intervention is required, the investigator in charge of the centre will report the monitor, the sponsor and the main researcher, and decide whether or not to make an emergency appearance.

Record for First-level blinded code : the first-level of drug blind code is identify the person who is assigned to the drug Group, second-level blind code is identify the person who is assigned to each dosage of drug group of the 80mg, 160mg and placebo group. Both level of blinded code will keep in sealed envelop respectively in site and sponsor.

Blind rule: Sponsors, researchers, data managers, and statisticians together under the blind to complete all research data audit and lock database, and then start to first-level unblinding, and the statisticians to perform the statistical analysis; after the completion of the preliminary draft of the statistical analysis report, perform a second-level unblinding.

Any modification of the database after the unblinding need to obtain the agreement from the principal investigator, the statisticians, the data manager and sign and data together.

## **11. Data management and statistical analysis**

### **11.1 Data management**

All collected data must be entry and completed by site staff to EDC system.

Completed eCRFs are required for each subject who signs an informed consent. All data will be transmitted to the EDC system. Corrections are recorded in an audit trail once the data transmit to EDC system, the new information, identification of the person making the correction, the date the correction was made, and the reason for change.

If further changes are required, the relevant monitor or data Manager will open a queries in the EDC system. The queries will be answered by the relevant staff in the research center. The name of the person who answered the question, the time and date will be tracked for audit. Once all the original data has been checked and all questions have been answered, the monitor or data manager will freeze the eCRF page

A handbook will be provided to the research center in regard how to entry the data and how to answer the queries in the EDC system. In addition, the EDC system training will be provided to the research Centre staff.

The sponsor or its designee will be permitted to review the subject's medical and hospital records pertinent to the study to ensure accuracy of the eCRFs.

The researcher ( the authorized personnel) will be permitted to access the EDC system. The system is used to collect clinical research data electronically.

The EDC system access controls will be set to decide who can get into a system and what tasks they can perform, Generally, only researchers and authorized personnel can enter and correct data on eCRF.

It is necessary to correct the inconsistency of clinical data by computer logic checks as well as manual examination. The quires will be open in the system, and the site staff will be notified that new queries need to be answer online. All correction will be made directly online by the relevent researcher or authorized personnel. Source data verification and cross-check will be performed to ensure the consistency between the data entered at different time and different modules to ensure the quality of the data.

The researchers must electronically sign and data after completion.

The data management plan will be performed at the begining of the study, which will include detailed requirements for how to ensure the data are consistent and accurat, and how to clearlying the error data. The database will be updated according to signed data correction.

